#### Chronic illness checklist

A 16-item checklist of chronic health conditions will provide the type and number of conditions reported by participants [55]. The checklist includes conditions related to musculoskeletal pain, arthritis, headaches, cardiovascular disease, asthma, stomach disorders, mental disorders, diabetes, and handicaps.

### Process evaluation

A process evaluation will be conducted alongside the randomized controlled trial to gain insight into the feasibility of this intervention for more widespread dissemination and to detect any particular study challenges that might be identified from more qualitative assessments. The process evaluation will be based on the RE-AIM framework, which consists of five dimensions: Reach, Efficacy/effectiveness, Adoption, Implementation, and Maintenance [56]. The goals of the process evaluation will be to assess the reach of the program (at both the employer and participant level), to identify any dose–response relationships between levels of participation and outcomes, to evaluate adherence to the study protocol, to assess the satisfaction and experiences of workers and facilitators, and to identify facilitators and barriers for future implementation. Information will be collected by quantitative as well as qualitative methods. In the final follow-up survey, participants will be asked whether they might be willing to participate in an in-depth interview that would include the topics shown above. Since it is not feasible to interview all stakeholders, purposeful sampling will be applied based on relevant characteristics of the target population in combination with the answers to the questionnaire.

### Sample size

The estimated effect size for the primary outcome measure (Work Limitations Questionnaire) is based on the size of effect obtained in a prior intervention trial focusing on workers with depression [38]. In that study, the effect size for various WLQ subscales ranged from 0.51 to 0.87 standard deviation units, suggesting a medium effect size, *f* = 0.25. With a target recruitment of 300 volunteers (60 from each organization), an assumed attrition rate of 20 %, and an alpha level of 0.05, the statistical power to detect a medium effect size (*f* = .25) on the primary outcome measure is 0.96 without consideration of the nested design or the possible need for covariates when making pre-post group comparisons. However, given the possible complication of non-equivalent treatment sites and the inclusion of several covariates in the final group comparison [57,58], a power estimate in the range of 0.80 – 0.85 would be a more conservative estimate based on various scenarios simulated in the PASS 11 Power Analysis & Sample Size Software [59].

### Data collection procedure

After providing informed consent, participants will complete a baseline survey and then be assigned to the intervention or control arms using a block randomization schedule (blocked in groups of 20) maintained privately by the project statistician. Six and 12 months after initial recruitment, participants will be mailed a follow-up survey (or provided access to an on-line survey) to provide for re-assessment of primary and secondary outcome measures. Non-responders will be sent two additional reminders, and all participants will receive a payment of $50 for completing each of the 3 research survey assessments (baseline, 6 months, 12 months).

### Statistical analyses

The primary analytic strategy will be to compare the intervention and control groups on changes in outcome measures at 6- and 12-month follow-up using a multilevel linear mixed model that will take into account the employer and the 3 repeated measurements, and also allow for missing data on either the 6- or 12-month assessment. The two primary outcome measures will be work limitations (total work productivity index from the Work Limitations Questionnaire) and work engagement (total score from the Utrecht Work Engagement Scale). Because of the nesting of participants within 5 different employers, a multilevel analysis will be necessary with employer treated as a fixed factor. This will help to account for any systematic differences in the working populations, job demands, and policies and practices within these organizations. We also anticipate the inclusion of at least 3 individual-level covariates (e.g., age, gender, and number of chronic conditions) in the principal analysis if there are relevant group differences at baseline.

A number of background variables will be assessed to check that the randomization has yielded equivalent comparison groups at baseline. Background variables will include: age, gender, level of education, income, number and type of chronic conditions, blue-collar versus white-collar jobs, job stress, hours of work per week, shift work, number of household dependents, and job and industry tenure.

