### Study design

The proposed study design is a randomized, controlled trial (RCT) of an employer-sponsored psycho-educational group intervention program designed to improve workplace functioning among workers with chronic physical health symptoms (Clinical Trials Registry # NCT01978392). The study methodology involves recruiting employees with chronic conditions from five worksites, randomizing them to participate in a group intervention program or to a wait-list control arm, and assessing changes in baseline worker engagement and work limitations at 6- and 12-month follow-up. We hypothesize that group participation will improve health and disability outcomes by improving self-efficacy beliefs in several work-related domains (see Figure 1). A process evaluation will be conducted alongside the RCT. The study has been reviewed and approved by the Dartmouth College Committee for the Protection of Human Subjects (#24084).

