### Randomization and blinding

Randomization will occur at the individual level after workers provide written informed consent and complete the baseline survey. As recruitment of workers will occur over a period of time, a computer-generated block randomization schedule (with equal sized groups for every 20 participants) will be maintained by the project statistician and used to assign individuals to the intervention or control conditions, and separate randomization schedules will be maintained for each of the five participating employers. Allocation will be concealed and the randomization schedules will be kept confidential and secured by the project statistician, so group assignment will not be anticipated by those involved in patient recruitment. The research associate responsible for collecting and compiling follow-up survey data and the researchers performing data analyses will be kept blind to group assignment. The nature of the psycho-educational group intervention will make it impossible to blind study participants or group facilitators from randomization results.

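### If baseline means are left free by arm, comparing changes from baseline gives away precision on both primary outcomes that a baseline-constrained model would recover at essentially no cost

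*Protocol article*

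**What the plan says.** Under Statistical analyses the protocol article plans to "compare the intervention and control groups on changes in outcome measures at 6- and 12-month follow-up". The two primary outcomes are the WLQ productivity index and the UWES total score. Estimation is to be done "using a multilevel linear mixed model that will take into account the employer and the 3 repeated measurements", and employer is a fixed factor. Baseline is therefore one of the modelled responses, and the treatment effect is described as a between-arm difference in change.

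Two other places describe the comparison in the same terms. Study design speaks of "assessing changes in baseline worker engagement and work limitations at 6- and 12-month follow-up", and Sample size refers to covariates that may be needed "when making pre-post group comparisons".

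The same section expects at least three individual covariates, with age, gender and number of chronic conditions as examples, to enter "in the principal analysis if there are relevant group differences at baseline". The baseline WLQ or UWES score is neither among these examples nor among the background variables to be checked for balance. The text does not say whether the mixed model has an arm difference at baseline or a common baseline mean.

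Randomization and blinding fixes the order of events: "Randomization will occur at the individual level after workers provide written informed consent and complete the baseline survey". Allocation is 1:1 in blocks ("with equal sized groups for every 20 participants"), with a separate schedule for each employer.

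**The concern.** A difference in change is commonly obtained from a mixed model with group, time and group-by-time terms. That model estimates a separate baseline mean for each arm and subtracts the estimated baseline difference in full from the follow-up difference. Here the baseline survey precedes randomization, so the expected baseline means are equal by design and any observed difference is chance. Estimating a quantity known to be zero, and then subtracting it, adds noise.

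Two consequences follow if the model is fitted that way. The standard errors at 6 and 12 months are larger than they need to be on both primary outcomes. And given a chance baseline difference δ between arms, regression to the mean implies that only ρδ is expected to carry through to follow-up. Subtracting δ over-corrects by (1 − ρ)δ.

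Precision matters here because the protocol's own cautious power estimate is only 0.80 to 0.85.

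**Working it through.** **Inputs from the protocol.** 300 recruited, 1:1 allocation, 20% attrition (so 240 analysed, 120 per arm), α = 0.05 (sidedness not stated; two-sided taken here), effect size f = 0.25, stated power 0.96, cautious power 0.80–0.85. **Not in the protocol:** the baseline-to-follow-up correlation ρ, and the SD of change. Every value of ρ below is an assumption.

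**1. The plan's own figure.** For two equal groups d = 2f = 0.50. The standard error in SD units is √(2/120) = 0.1291, so 0.50/0.1291 = 3.873. Power = Φ(3.873 − 1.96) = Φ(1.913) = 0.972. A noncentral F with λ = 240 × 0.25² = 15 gives 0.971. The stated 0.96 is reproduced to about one point.

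**2. Complete data.** With equal variances over time, the per-participant variance in units of SD² is:
- difference in change (free baseline means): 2(1 − ρ)
- baseline-constrained or baseline-adjusted: 1 − ρ²

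The ratio is (1 − ρ²)/[2(1 − ρ)] = (1 + ρ)/2, so the reduction is (1 − ρ)/2. It is positive for every ρ below 1. For ρ below 0.5, 2(1 − ρ) exceeds 1, so the change contrast is noisier than ignoring baseline altogether.

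**3. With the plan's attrition.** Suppose a fraction p = 0.8 of each arm of n has all three visits and the rest have a baseline only, with compound symmetry. In units of SD², the variance of the arm contrast at a follow-up visit is:
- constrained: 2(1 − ρ²)/(np)
- unconstrained: 2(1 − ρ²)/(np) + 2(1 − ρ)²/n

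The reduction is therefore p(1 − ρ)/[(1 + ρ) + p(1 − ρ)], which returns (1 − ρ)/2 when p = 1. At ρ = 0.5 it is 0.40/(1.50 + 0.40) = 0.21. At ρ = 0.9 it is 0.08/(1.90 + 0.08) = 0.04.

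| ρ (assumed) | Change | Constrained | Reduction, complete data | Reduction, 20% baseline only |
|---|---|---|---|---|
| 0.3 | 1.40 | 0.91 | 35% | 30% |
| 0.5 | 1.00 | 0.75 | 25% | 21% |
| 0.7 | 0.60 | 0.51 | 15% | 12% |
| 0.9 | 0.20 | 0.19 | 5% | 4% |

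The relevant ρ is the correlation between baseline and the visit in question. If correlation decays with time, the gain is larger at the later visit. With first-order autoregressive correlation of 0.7 between adjacent visits, the baseline-to-12-month correlation is 0.49 and the complete-data reductions are 15% at 6 months and 25.5% at 12 months.

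**4. What it could mean for power.** For a variance reduction r, power moves from P to Φ[(1.96 + z_P)/√(1 − r) − 1.96], where z_P is the standard normal quantile at P.

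| Starting power | r = 5% | r = 15% | r = 25% |
|---|---|---|---|
| 0.80 | 0.82 | 0.86 | 0.90 |
| 0.85 | 0.87 | 0.90 | 0.93 |
| 0.96 | 0.97 | 0.98 | 0.99 |

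These rows assume that the starting power belongs to an unconstrained change contrast, which the protocol does not say.

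**The case against.** The strongest reply is that the plan does not commit to the inefficient model. A constrained longitudinal model also uses three repeated measurements, and its arm effect at follow-up is also a between-group difference in change. The planned sentence fits either. Nor is the absence of the baseline score from the covariate examples telling by itself, since a baseline modelled as a response would not also be listed as a covariate. A reader might infer from the word *changes* that baseline means are left free by arm. The text does not establish that, so the loss is conditional on the parameterisation. One might add that such coding is normally settled in a statistical analysis plan.

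That reply sets the limits of the point without removing it. The article does state the primary contrast as a comparison of changes, and it does fix a covariate rule that depends on observed imbalance. Neither makes use of the baseline score in the way randomization allows, and the conventional fit of that description is the less precise one.

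A reader might also infer that the change analysis is biased or invalid. It is not: under randomization it is unbiased and its test is valid. The over-correction is conditional on a chance baseline difference, and with 300 participants allocated in blocks within employer that difference should usually be small.

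Finally, the gain depends wholly on ρ and is modest if ρ is high. Starting from the headline power of 0.96 it adds only one to three points.

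**Conclusion.** The point holds as a free improvement in efficiency. If the primary model leaves baseline means free by arm, its 6- and 12-month contrasts carry avoidable variance on both primary outcomes. The saving is (1 − ρ)/2 with complete data: 35% to 5% for ρ from 0.3 to 0.9. It is about 30% to 4% when 20% of participants have a baseline only, under compound symmetry.

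A flat saving of 15–25% is a tempting summary, but it describes only complete data with ρ between 0.5 and 0.7, and the protocol gives no correlation to support it. With the plan's attrition that same range of ρ gives about 21% to 12%.

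The conclusion rests on three things: the baseline survey preceding randomization, which the protocol states; equal variances over time, which is assumed; and the usual group-by-time parameterisation, which the protocol neither states nor rules out.

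**What to change.** State in the analysis section that, for both the WLQ productivity index and the UWES total score, the primary mixed model:
- takes all three time points as responses, with a baseline mean common to both arms;
- has arm effects only at 6 and 12 months, with employer as a fixed factor;
- applies this constraint whatever baseline difference is observed.

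The planned estimand, a between-arm difference at each follow-up, is unchanged. The constraint removes a parameter and keeps every randomized participant who has a baseline.

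An alternative is a mixed model for the 6- and 12-month scores with the baseline score by time as a covariate, again regardless of imbalance. It is closely similar but not identical. It uses only participants with at least one follow-up, and it costs about one degree of freedom per time point. At 240 analysed, one degree of freedom is worth about 1/236, or 0.4% of the variance.

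Either change is a matter of wording and model specification. No extra data, visits or participants are needed.

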### Group intervention strategy

Participants randomized to the intervention arm will be assigned to participate in five 2-hour group workshop sessions (or ten 1-hour sessions, if necessary to meet scheduling constraints) led by a specially trained facilitator (licensed psychologist or clinical social worker) and provided over a span of approximately 2–3 months. The sessions will be offered at the work site but not during working hours. The content of the intervention was developed from qualitative studies [30] and from a review of existing self-management intervention elements [29], then piloted and revised according to participant feedback. The intervention incorporates standard elements of existing evidence-based pain and illness self-management efforts but tailors key messages and discussion elements to workplace problems most relevant to workers with chronic physical health conditions. The theoretical basis for the intervention (Figure 1) is Bandura’s Self-Efficacy component of Social Cognitive Theory, which suggests that “the self-assurance with which people approach and manage difficult tasks determines whether they make good or poor use of their capabilities” (p. 35) [34]. Each session is focused on different self-management strategies, with each session containing a mix of facilitator presentation, group discussion, case illustrations, role play, completion of in-session self-assessments and activities, and brief homework assignments. Participants are encouraged to support each other through communications outside of the scheduled meetings, though this interaction is voluntary. Approximately equal time is allocated to the topics of improving comfort, modifying work, communicating effectively, applying systematic problem-solving strategies, and dealing with negative thoughts and emotions (see Table 1).

**Table 1 T1:** Goals and key points for group sessions of the self-management intervention

	**Title**	**Session goals**	**Key points**
Session I	Self-management principles for coping with chronic pain and fatigue	Provide introductions; establish rapport; provide a scientific and philosophical rationale; differentiate self-management from medical management; recognize workplace challenges and constraints; set the general scope and agenda for future sessions	• Chronic physical health conditions are common.
			• Coping at work can require special skills.
			• Thoughts, emotions, and behavior play a part.

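### The stated analysis model has no workshop-group term, so the treatment effect's standard error is too small if outcomes correlate within workshops

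*Protocol article*

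**What the plan says.** All references are to the Protocol article.

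- **Randomization and blinding:** allocation is by individual, 1:1, in blocks of 20 with a separate schedule for each of the five employers. The data analysts are to be blind to assignment.
- **Group intervention strategy:** the intervention is a series of facilitator-led group sessions with discussion and role play. Contact between members goes further: "Participants are encouraged to support each other through communications outside of the scheduled meetings".
- **Non-treatment control strategy:** controls receive nothing until after their 12-month follow-up, so they form no groups before the outcomes are measured.
- **Statistical analyses:** the arms are compared "using a multilevel linear mixed model that will take into account the employer and the 3 repeated measurements". The reason given for a multilevel analysis is nesting within five employers, and employer is a fixed factor. Neither workshop nor facilitator is mentioned.
- **Sample size:** power is 0.96 before nesting and covariates are considered. It is then lowered to 0.80-0.85, "given the possible complication of non-equivalent treatment sites and the inclusion of several covariates in the final group comparison", on the strength of simulated scenarios that are not described. Workshop groups are not named here either.

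**The concern.** This is a partially nested design: participants share a facilitator, discussions and peer contact in one arm only. A workshop that goes well or badly moves all its members together, and no control group moves with it. That variation therefore enters the treatment contrast directly.

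Employer as a fixed factor removes differences between employers that are common to both arms, and stratified randomisation already balances those. It does not remove variation that exists only among treated workers.

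If such variation is present and not modelled, confidence intervals for the treatment effect are too narrow and p-values too small, which favours declaring a benefit. Recruiting more people into workshops of the same size does not cure this. The power statement has a matching gap: its discount is attributed to sites and covariates, and the clustering specific to this design is not mentioned.

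**Working it through.** **Inputs from the article (Sample size).** "With a target recruitment of 300 volunteers (60 from each organization"), 20% attrition, and "an alpha level of 0.05" (two-sided assumed). The effect size comes from a depression trial in which "the effect size for various WLQ subscales ranged from 0.51 to 0.87 standard deviation units", "suggesting a medium effect size, *f* = 0.25". For two equal arms d = 2f = 0.50. Analysed: 300 × 0.8 = 240, or 120 per arm.

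**Inputs that are assumptions.** Workshop size m = 8 to 10 analysed, and ICC 0.01 to 0.10. Each employer contributes 60 / 2 × 0.8 = 24 analysed intervention participants, so m = 8 means 3 workshops per employer (15 in all) and m = 10 means 12 in all. The check uses a single follow-up comparison, not the full repeated-measures model.

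**Step 1: the plan's own figure.** Naive SE = √(2/120) = 0.129 SD. Power = Φ(0.5/0.129 − 1.96) = 0.972; the noncentral t with 238 df gives 0.971. The stated 0.96 is reproduced to within about a point.

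**Step 2: error rate when workshops are ignored.**
- Design effect in the intervention arm: DE = 1 + (m − 1) × ICC.
- True SE = √((DE + 1)/120), so the variance ratio is (DE + 1)/2.
- True two-sided error = 2[1 − Φ(1.96/√ratio)].
- Example, m = 8, ICC 0.05: DE = 1.35, ratio = 1.175, error = 2[1 − Φ(1.808)] = 0.071.

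| ICC | Ratio, m = 8 | Error, m = 8 | Ratio, m = 10 | Error, m = 10 |
|---|---|---|---|---|
| 0.01 | 1.035 | 0.054 | 1.045 | 0.055 |
| 0.02 | 1.070 | 0.058 | 1.090 | 0.061 |
| 0.05 | 1.175 | 0.071 | 1.225 | 0.077 |
| 0.10 | 1.350 | 0.092 | 1.450 | 0.104 |

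The true SE is 1.02 to 1.20 times the naive one. A simulation of 20,000 trials (15 workshops of 8, employer fixed) gave 0.052, 0.056, 0.070 and 0.093 at ICC 0, 0.02, 0.05 and 0.10, in line with the formula and confirming that the fixed employer term does not absorb the effect.

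**Step 3: power when workshops are allowed for.** Power = Φ(0.5/SE − 1.96) with the true SE runs from 0.968 (m = 8, ICC 0.01) to 0.896 (m = 10, ICC 0.10). Under a conservative t reference with number of workshops minus 1 df, it runs from 0.942 to 0.833.

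**Step 4: can sites and covariates explain 0.80-0.85?** Under the fixed-employer model they change only the error df: power is 0.9711 at both 238 and 227 df. The needed variance inflation is 15/(1.96 + z)², where 15 = 0.5²/(2/120). This is 1.67 for power 0.85 and 1.91 for 0.80, which additive site differences and covariates do not produce. Two other routes could:
- Treatment effects that vary between employers, with employers treated as random. Setting τ²/5 = (inflation − 1) × 2/120 gives τ of about 0.24 to 0.28 SD.
- Workshop clustering with an ICC of about 0.15-0.20 (m = 10) or 0.19-0.26 (m = 8).

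**The case against.** **The inflation is conditional.** A reader might infer that type I error is inflated for every outcome. The article does not support that. It gives no ICC and no workshop size, the ICC may differ by outcome, and at 0.01 the excess is slight. Moreover, if the workshops affect nobody, individual randomisation keeps the test at its level. The error rates above apply when the average effect is zero but workshops differ in their effect. This stands. Under a real effect that varies between workshops, the intervals are still too narrow.

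**The blocks of 20 do not give workshop size.** The wording "with equal sized groups for every 20 participants" describes balance between arms within a randomisation block. Nothing links a block to a workshop, so it is no evidence for workshops of 10.

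**The power discount cannot be called wrong outright.** A reader might infer that 0.80-0.85 was wrongly derived, or that the trial is underpowered. The scenarios are not described, and variation of the treatment effect between sites could produce the fall. What can be said is that additive site differences and covariates do not, under the fixed-employer model. Power allowing for workshops lies within or above 0.80-0.85 in the range examined, so no shortfall is shown.

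**An article condenses.** Details of random effects and degrees of freedom are commonly left to an analysis plan. That carries limited weight here, because the article itself names the levels of the primary model and gives employer nesting alone as the reason for them.

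**Conclusion.** The point holds as a conditional defect in the stated analysis model: it omits the one level of clustering that exists in the intervention arm only. If the workshop ICC is above zero, the standard error is understated by a factor of about 1.02 to 1.20. A nominal 5% test then has a true error from about 0.054 (ICC 0.01, 8 per workshop) to 0.104 (ICC 0.10, 10 per workshop). This becomes material at an ICC of about 0.05 or more. Shared facilitators and encouraged peer contact give no ground for assuming zero.

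The power statement should name workshop clustering, but the sample size is adequate for workshops of 8 to 10 and ICC up to 0.10. That rests on the group size: at 12 per workshop and ICC 0.10 the conservative reference gives 0.79. The matter should be fixed; it does not call the design into question.

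**What to change.** - **Data:** record a workshop identifier for each intervention participant prospectively.
- **Model:** fit a partially nested mixed model with a random workshop effect in the intervention arm only, arm-specific residual variance, and Satterthwaite or Kenward-Roger degrees of freedom. Keep employer fixed.
- **Sample size section:** give power with workshop clustering at a stated group size and over a range of ICC (0.01 to 0.10). Also state what the simulated scenarios behind 0.80-0.85 assumed, in particular whether the treatment effect was allowed to vary between employers.

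**Cost.** One extra variable, one extra random term and slightly wider intervals; no extra recruitment. There is one conflict to manage: an identifier that exists in one arm only reveals assignment to analysts who are meant to be blind. The model code should therefore be fixed before the identifier is released to them.

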**Methods:**

In a randomized controlled trial (RCT), workers participating in an employer-sponsored self-management group intervention will be compared with a no-treatment (wait list) control condition. Volunteer employees (n = 300) will be recruited from five participating employers and randomly assigned to intervention or control. Participants in the intervention arm will attend facilitated group workshop sessions at work (10 hours total) to explore methods for improving comfort, adjusting work habits, communicating needs effectively, applying systematic problem solving, and dealing with negative thoughts and emotions about work. Work engagement and work limitation are the principal outcomes. Secondary outcomes include fatigue, job satisfaction, self-efficacy, turnover intention, sickness absence, and health care utilization. Measurements will be taken at baseline, 6-, and 12-month follow-up. A process evaluation will be performed alongside the randomized trial.

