### Primary outcome measure

#### Work limitation

The Work Limitations Questionnaire (WLQ) [35] is a 25-item self-report questionnaire that assesses the degree to which working individuals are experiencing limitations on-the-job due to their health problems and health-related productivity loss. The WLQ items ask respondents to rate their level of difficulty or ability to perform specific job demands. Items are grouped into 4 scales: (1) time management, (2) physical demands, (3) mental-interpersonal demands, and (4) output demands. The individual scales have shown good internal consistency (Cronbach’s alpha > .70) and they have been validated against other health and disability constructs [36]. Most importantly for the current study, the WLQ has been correlated with objectively-measured employee-level work productivity, and scores on the WLQ can be translated into a single Productivity Index score that indicates the percentage difference in output from a healthy (not limited) benchmark population [37]. Recently, the WLQ has also been shown sensitive to the effects of intervention [38].

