### Secondary outcome measures

#### Work engagement

The Utrecht Work Engagement Scale (UWES) is a 17-item self-report questionnaire that was designed to measure the degree to which employees have a sense of energetic and effective connection with their work activities (energy, involvement) and see themselves as able to deal with the demands of their job (professional efficacy) [39]. We will use the shortened 9-item version which has been previously validated [40]. Respondents rate their level of agreement with stated feelings about work on a 7-point likert scale from “never” to “always”. Originally conceptualized as the opposite of job burnout, work engagement has begun to receive a high level of attention in organizational research, and work engagement questions are now commonplace in large-scale employee opinion surveys. Work engagement has been defined as a positive, fulfilling, work-related state of mind that is characterized by vigor, dedication, and absorption. We chose this outcome measure because our prior qualitative work showed that disengagement from work was a greater concern to workers with health issues than any lapse in productivity.

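### The protocol makes work engagement a secondary outcome in one place and a co-primary outcome in another, and its power calculation fits only the single-primary version

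*Protocol article*

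**What the plan says.** Three places support a single primary outcome:

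- In the outcome definitions, the heading "Primary outcome measure" is singular and only the WLQ stands under it.
- Work engagement, measured by the nine-item UWES, is the first measure under the heading "Secondary outcome measures".
- The Sample size section again uses the singular: "The estimated effect size for the primary outcome measure (Work Limitations Questionnaire) is based on the size of effect obtained in a prior intervention trial". Its power figure uses "an alpha level of 0.05", and no power is given for the UWES.

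Two places support two primary outcomes:

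- The Abstract (Methods) states: "Work engagement and work limitation are the principal outcomes". Its list of secondary outcomes leaves engagement out.
- The Statistical analyses section states: "The two primary outcome measures will be work limitations (total work productivity index from the Work Limitations Questionnaire) and work engagement".

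On timing, the analysis will "compare the intervention and control groups on changes in outcome measures at 6- and 12-month follow-up using a multilevel linear mixed model". Neither follow-up time is singled out. The text does not say whether the comparison is one joint test per outcome or a separate test at each time.

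**The concern.** The status of work engagement is not left open for a later document to settle. It is fixed twice, in opposite ways. If the WLQ shows no difference and the UWES does, the Statistical analyses section supports reporting a positive primary result, while the outcome and Sample size sections make the same result secondary. A reader of the final report could not tell from this document which applies.

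Two things follow. The stated power may not belong to the criterion by which the trial will be judged. The chance of a false positive claim also cannot be given as one number, because it changes with the reading chosen.

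**Working it through.** **1. Which version does the stated power describe?**

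Inputs from the Sample size section: 300 recruited, 20% attrition, f = 0.25, alpha 0.05, stated power 0.96. Allocation is equal (Randomization and blinding). Sidedness is not stated, so two-sided is assumed.

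- Analysed: 300 × 0.80 = 240, or 120 per arm.
- For two equal groups d = 2f = 0.50.
- Expected z = d × √(n/2) = 0.50 × √60 = 3.873.
- Power (normal) = Φ(3.873 − 1.960) = Φ(1.913) = 0.972. The noncentral t gives 0.971.

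Both are close to the stated 0.96. A one-sided test gives 0.987 and 150 per arm gives 0.991, which fit less well. The stated figure is therefore that of one two-sided 0.05 test on one outcome, which is the single-primary version.

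**2. False-positive rate under each reading**

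The document gives no correlation between outcomes or between time points. The correlations below are assumptions, shown as ranges. All tests are two-sided at unadjusted 0.05. The correlated cases were simulated with 1,000,000 draws each.

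| Reading | Chance of at least one false positive claim |
|---|---|
| WLQ only, one test | 0.05 |
| Both outcomes required, one test each | at most 0.05 |
| WLQ only, either of two separate times (correlation 0.5 to 0.7) | 0.084 to 0.091 |
| Either outcome, one test each, independent | 1 − 0.95² = 0.0975 |
| Either outcome, one test each (outcome correlation 0 to 0.7) | about 0.084 to 0.098 |
| Any of four tests (time correlation 0.5 to 0.9, outcome correlation 0 to 0.7) | 0.115 to 0.173 |
| Any of four tests, independent | 1 − 0.95⁴ = 0.185 |

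One test per outcome covers both a single time point and a joint two-degree-of-freedom test over the two times. The simulated results for these were nearly the same.

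**3. Power if both outcomes stay primary and alpha is divided**

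At 0.025 two-sided the critical value is 2.241.

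- Unadjusted calculation: Φ(3.873 − 2.241) = Φ(1.632) = 0.949; noncentral t 0.946, against 0.971 at 0.05.
- From the protocol's conservative 0.80: implied expected z = 1.960 + 0.842 = 2.802; Φ(2.802 − 2.241) = 0.71.
- From 0.85: implied expected z = 1.960 + 1.036 = 2.996; Φ(2.996 − 2.241) = 0.77.

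The loss is about 2.5 points from the unadjusted figure, but about 8 to 9 points from the conservative estimate.

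**The case against.** The strongest reply is that much of what seems missing belongs in an analysis plan. A multiplicity procedure, a success rule and a primary contrast are commonly left there, this is a condensed journal article, and the plan is not shown. That stands: their absence is no finding here. It does not remove the contradiction, because each section states a definite outcome status and the two are incompatible.

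A reader might go further and infer that the trial tests both outcomes at both times, each at 0.05, so that its false-positive rate is about three times nominal. The document does not support that:

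- The 0.05 appears once, as an input to the WLQ power calculation.
- No section says that four separate tests are run or that any one of them would make the trial positive.
- The mixed model takes in all three measurements and can equally be read as one group-by-time test per outcome.
- The hypothesis at the end of the Background joins the two outcomes with an 'and'. This is not a decision rule, but it fits a both-required reading at least as well, and with one test each that keeps the error at 0.05 or below.
- A figure near 0.15 needs both the any-of-four rule and assumed correlations.

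The registry entry is not visible either, so nothing can be said about whether it already settles the matter or needs updating.

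**Conclusion.** The contradiction holds and should be fixed. The two outcome headings and the Sample size section describe one primary outcome; the Abstract and the Statistical analyses section describe two. Nothing in the document reconciles them.

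Its size is best put as a conditional range: nominal or lower under the strictest readings, up to about twice nominal when either of two outcomes suffices, and 2.3 to 3.7 times nominal only under an any-of-four rule that is nowhere stated. The upper rows rest on assumed correlations, and all rows assume two-sided tests. The case for correction rests on the conflicting outcome status and the mismatch with the power calculation, not on any one error rate.

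**What to change.** Give work engagement the same status in the Abstract, the two outcome sections, the Sample size section and the Statistical analyses section. There are two workable routes.

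1. **WLQ as sole primary (least costly).** Keep the WLQ productivity index as the only primary outcome, which matches the sample size. Test the UWES total at 0.05 only if the WLQ is significant. Amend the Abstract and the Statistical analyses section. The WLQ loses no power.
2. **Two primaries.** Move the UWES out of the secondary section, state the success rule (for example Holm, with 0.025 at the first step) and restate power for it. At 0.025, WLQ power falls from 0.971 to 0.946 in the unadjusted calculation, and from 0.80–0.85 to about 0.71–0.77 on the conservative estimate. Power for the UWES would need its own assumed effect, which the document does not give.

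Under either route, name one confirmatory contrast per outcome: a single time point or a joint group-by-time test. The document treats 6 and 12 months alike and gives no ground for preferring one, so that choice is the sponsor's. Route 1 costs only wording; route 2 also needs a new power statement.
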